**UPDATES TO THE PROTOCOL:**

**Cover Page (p. 1)**

- The study title has been updated to reflect the change from a Phase II to a Phase II/III as follows:  
The Janus Rectal Cancer Trial: A randomized phase II/III trial testing the efficacy of triplet versus  
doublet chemotherapy regarding to achieve clinical complete response and disease-free survival in  
patients with locally advanced rectal cancer.

### Cover Page for Data Submission (p.3)

- The following information has been removed from the Data Submission column: ~~Do not submit study data or forms to the CTSU. Do not copy the CTSU on data submission.~~

### Schema (P. 4)

- The title on the schema page has been updated to reflect the change from a Phase II to a Phase II/III.
- Study schema has been update to reflect that patients will be followed for 5 & 8-years.

### Section 1.0 (Background)

- In [section 1.1 \(Total Neoadjuvant Therapy \(TNT\) Strategy\)](#), the 8th paragraph has been updated with more background information as follows: 'Importantly, the 7-year updated data from PRODIGE23 presented at ASCO 2023 demonstrated significantly better DFS, metastasis-free survival and overall survival in the TNT-arm versus the standard of care arm (68% vs. 63% DFS). These data support the use of a triplet TNT approach to improve DFS outcome for rectal cancer patients.'
- In [section 1.4. \(Rationale for use of the consolidation TNT approach for the Janus Trial\)](#), the second paragraph has been updated with more data as follows: 'Of note, 5-year data in the OPRA trial has since resulted and demonstrated stable organ preservation rates for the CNCT arm (54%) versus 39% in the INCT arm (p=0.012). Further, local regrowth rates remained lower in the CNCT arm (29%) versus 44% in the INCT arm (p=0.02).'

### Section 2.0 (Objectives)

- In [section 2.1 \(Primary Objectives\)](#), a second paragraph has been added to reflect the studies expansion to a Phase II/III: 'Phase III: To evaluate and compare disease-free survival (DFS) in patients with locally advanced rectal cancer treated with neoadjuvant LCRT followed by neoadjuvant mFOLFIRINOX versus neoadjuvant LCRT followed by neoadjuvant mFOLFOX6.'
- In [section 2.2 \(Secondary Objectives\)](#), 2.2.2 has been deleted: ~~To evaluate and compare the disease-free survival (DFS) time between the two treatment arms.~~ and the other objectives have been renumbered.

### Section 4.0 (Patient Registration)

- CTSU template language has been updated as required.

### Section 5.0 (Study Calendar)

- **Arm 1 and Arm 2 Study Calendars**
  - A header has been added to the Arm 1 and Arm 2 study calendars.
  - a second sentence was added to Footnote \*: 'As such, exact week number from registration may vary and as such can be adjusted to reflect timing of start of chemotherapy.'
  - the study week has been update from ~~week 30-36~~ to weeks '32-38.'
  - the following tests and procedures have been added 'History, physical, height and adverse event assessments' In addition, a new footnote \*\* has been added to define what has to be collected during the history and physical assessment as follows: 'Weight, Pulse, BP, Performance Status. Performance Status will only be required at pre, week 10 and weeks 32-38' and the old footnote \*\* is now footnote \*\*\*.
  - the definition of DRE (digital rectal exam) has been added for clarity.

- footnote \*\*\*\* has been added: ‘For women of childbearing potential (see Section 3.2.3). Must be done ≤ 7 days prior to registration.’
- Footnote 3 has been revised to clarify the Med Onc visit: ‘Patients will be seen and evaluated during neoadjuvant chemoradiation and chemotherapy with necessary laboratory evaluations per institutional guidelines. For neoadjuvant chemotherapy, recommendation is to be evaluated by medical oncology during (Arm 1) and (Arm 2) chemotherapy every two weeks (every three weeks for patients getting CAPOX) or as needed per institutional guidelines. In patients not seen and evaluated by medical oncology every cycle, adverse events must still be collected and reported every cycle by relevant research staff.’ ~~Patients will be seen and evaluated by medical oncology during (Arm 1) and (Arm 2) chemotherapy every two weeks (every three weeks for patients getting CAPOX) or as needed per institutional guidelines. In patients not seen and evaluated by medical oncology every cycle, adverse events must still be collected and reported every cycle by relevant research staff.~~
- **(Study Week 10)** footnote #7 has been added for clarification: ‘Assessment by surgeon, medical and radiation oncology occurs in a multidisciplinary fashion to ensure the patient has tolerated LCRT well and does not have to occur exactly at week 10; simply should occur prior to initiation of chemotherapy and is meant to ensure appropriate transition to the medical oncology team as they begin systemic chemotherapy.’
- The study calendars for [Evaluations during follow-up for WW patients](#) and [Evaluations during follow-up for TME patients](#) have been separated for ease of use for study sites.
- In the [WW study calendar](#) (**Footnote \*\***) has been changed to reflect that MRIs conducted during years 4 through 5 will only be covered if clinically indicated.
- In the [WW study calendar](#), (**Footnote 2**) the second sentence has been deleted as follows: After 36 months, CEA will be evaluated every 6 months up to five years, based on NCCN guidelines. ~~One additional 10 ml EDTA tube of blood will be collected at these time points for research purposes.~~

## **Section 6.0 (Data and Specimen Submission)**

- In [section 6.1](#) the CTSU template language has been updated as required.

## **Section 7.0 (Treatment Plan/Intervention)**

- In [section 7.1 \(Neoadjuvant Chemoradiotherapy\)](#)
  - new first and second sentences have been added as follows: ‘For specific questions or concerns regarding this section, please contact [name] [[contact]](mailto:[contact]) and/or [name] [[contact]](mailto:[contact]).’ and ‘Protocol treatment with long course chemoradiation therapy should be initiated within 28 days following protocol registration.’
  - the first sentence of the third paragraph has been revised as follows: During radiation, a fluoropyrimidine must be administered concomitantly (preferred capecitabine 1650 mg/m^2/d PO in two divided doses, ‘rounded as appropriately per institutional guidelines’...
  - a new second, third and fourth sentence has been added to the end of the third paragraph: ‘If in the opinion of the investigator, a toxicity is considered to be due solely to the radiation, then the radiation can be held at the investigator’s discretion. The rationale for treatment break and the duration of the break needs to be documented. Investigators are encouraged to reach out to [name] and/or [name] to discuss concerns with radiation toxicity resulting in a treatment break.’
  - the first sentence of the fourth paragraph has been revised: Note: Intensity modulated radiation therapy (IMRT) is permitted ~~If treatment includes the inguinal lymph nodes, IMRT is recommended.~~

- In [section 7.1 \(Clinical Target Volume\)](#) the fourth sentence has been revised: If the external iliac nodes or inguinal nodes are felt to be at risk for ‘micrometastases’ ~~involvement~~ by the radiation...and a new fifth sentence has been added” ‘If treating the inguinal lymph nodes prophylactically IMRT is required.’
- In [section 7.1.1\(Radiation Therapy Quality Assurance\)](#) the Protocol Dosimetrist’s email address has been hyperlinked.
- In [section 7.2 \(Consolidation Neoadjuvant Chemotherapy\)](#)
  - a new first sentence has been added for clarification: ‘For specific questions or concerns regarding this section, please contact [name] [[contact]](mailto:[contact]) and/or [name] [mailto:[name]\\[contact]](mailto:[contact]).’
  - the fifth paragraph has been revised as follows: ‘Infusion times, concurrent and/or order of drug administration for all chemotherapy in this protocol may be modified per institutional guidelines.’ ~~Administer drugs in the order listed, but infusion times for all chemotherapy in this protocol are per institutional guidelines.~~
- [Table 7.2.2 \(Treatment regimen for Control Arm \(CAPOX for 5 cycles\)](#) footnote b has been updated with the medication instructions from the medication diary: ‘Do not double up doses. If a dose is missed for any reason, skip the dose and take the next dose at the normal time.’ And footnote C has been updated with instructions regarding medication compliance as follows: ‘Sites may provide Use of patients with a patient pill diary (Appendix III) to record capecitabine compliance. However, it is NOT required. Non-English-speaking patients should be instructed to self-document their compliance.’
- In [section 7.3 \(Surgery\)](#) the sixth sentence of the first paragraph has been revised: ... endoscopy/DRE then endoscopy/DRE should take precedence in the decision making ‘on whether’ to proceed to WW or TME.

## [Section 8.0 \(Dose and Treatment Modifications\)](#)

- In [section 8.2 \(Dose Modifications\)](#) and new eighth paragraph has been added: ‘For specific questions or concerns regarding this section, please contact [name] [[contact]](mailto:[contact]) and/or [name] [mailto:[name]\\[contact]](mailto:[contact]). In the event of treatment-related AEs during consolidation chemotherapy that requires treatment hold for  $\geq 30$  days from the date of the planned cycle, consolidation chemotherapy should be discontinued. If consolidation chemotherapy is discontinued because of delay, patients the subject should be referred for presurgical restaging as detailed in the study calendar in section 5.0,’ and a new ninth paragraph has been added: ‘In the event of non-treatment related AEs that result in dose delays of 30-60 days and have resolved to grade  $\leq$  grade 1 by 60 days from the date of the planned cycle, patients may continue with consolidation chemotherapy if deemed in their best interest by the treating oncologist.’
- In [table 8.2.3.2](#) a minor formatting update has been made to the table instructions: Refer to footnote ‘a’ for management of anemia.
- In [section 8.2.4 \(Treatment Management of Patients on Chemoradiation\)](#) a NOTE has been added after [table 8.2.4.2](#): ‘NOTE: If in the opinion of the investigator, a toxicity is considered to be due solely to the radiation, then the radiation can be held at the investigator’s discretion. The rationale for treatment break and the duration of the break needs to be documented. Investigators are encouraged to reach out to [name] and/or [name] to discuss concerns with radiation toxicity resulting in a treatment break.’

## [Section 10.4 \(Leucovorin calcium\)](#)

- In the third paragraph of the Drug Interactions section, the drug name has been updated as follows: ‘Phenobarbital’ ~~PHENobarbital~~: Leucovorin Calcium-Levoleucovorin may decrease the serum concentration of ‘Phenobarbital’ ~~PHENobarbital~~

### Section 11.0 (Measurement of Effect)

- In [section 11.2.1](#) (Clinical and Radiologic Assessment) the link to the endoscopic and MRI educational video has been added: ‘[Please see CTSU website for endoscopic and MRI assessment of response video by [name]. Please contact [name] with questions about this section \(see face page for contact information\). Alliance A022104 \(JANUS\) Trial Webinar - October 2023 \(youtube.com\).](#)’
- In [section 11.2](#), (Clinical Tumor Evaluation prior to TME), the second sentence in the second paragraph has been updated to reflect that patients will be followed for 5 & years.

### Section 12.0 (End of Treatment/Intervention)

- In [section 12.3.1](#) (Duration of Follow-up) the table has been completely revised.

### Section 13.0 (Statistical Considerations)

- [Section 13.0](#) has been revised to reflect the studies expansion from a Phase II to a Phase II/III.

### Section 16.0 (References)

- References 44-48 have been added to reflect the studies expansion from a Phase II to a Phase II/III.

---

### UPDATES TO THE MODEL CONSENT:

- The **official study title** has been updated to reflect the change from a Phase II to a Phase II/III as follows: The Janus Rectal Cancer Trial: A randomized phase II/III trial testing the efficacy of triplet versus doublet chemotherapy ~~regarding to achieve~~ clinical complete response and disease-free survival in patients with locally advanced rectal cancer.
- Under ‘**What will happen if I decide to take part in this study?**’ the second and third sentences of the second paragraph have been updated: They will check you about every ‘3’-4 months for 2 years... and After that, they will check you about every 6 months for 3 years ‘up to 5 years.’
- Under ‘**What is the purpose of this study,**’ the second sentence of the third paragraph has been updated to reflect the change in the overall enrollment number from ~~342~~ to 760.
- Under ‘What are the study groups?’, the number of participants in each group has been updated from ~~156~~ to 380.
- Under the ‘**Drug Risks**’ the risk list for **capecitabine** has been updated with the most recent version dated October 12, 2023.
- Under ‘**Drug Risks**’ the risk list for **oxaliplatin** has been updated with the most recent version dated December 21, 2022.

**Replacement protocol and model consent documents have been issued.**

---

**Eligibility Criteria (see Section 3.2)**

- Clinical stage II or III rectal adenocarcinoma defined as T4N0, or any T with node positive disease (any T, N+); also T3N0 requiring APR or coloanal anastomosis
- No prior systemic chemotherapy, targeted therapy, or immunotherapy; or radiation therapy administered as treatment for colorectal cancer within the past 5 years
- Not pregnant and not nursing
- Age  $\geq 18$  years
- ECOG Performance Status 0-1
- No upper rectal tumors (distal margin of tumor  $> 12$  cm from the anal verge)
- No recurrent rectal cancer; prior transanal excision, prior distal sigmoid cancer with a low anastomosis
- No known mismatch repair deficient rectal adenocarcinoma

**Required Initial Laboratory Values**

|                             |                                                  |
|-----------------------------|--------------------------------------------------|
| ANC                         | $\geq 1500/\text{mm}^3$                          |
| Platelet count:             | $\geq 100,000/\text{mm}^3$                       |
| Creatinine:                 | $\leq 1.5 \times$ upper limit of normal (ULN) OR |
| Calc. creatinine clearance: | $\geq 50 \text{ mL/min}$                         |
| Total bilirubin:            | $\leq 1.5 \times$ ULN                            |
| AST/ALT:                    | $\leq 3 \times$ ULN                              |

**Schema**

[figure not shown]

\* Patients with locally advanced rectal cancer:  $\leq 12\text{cm}$ , T4N0 OR anyT, N+ OR T3N0 that would require APR or coloanal anastomosis

\*\* LCRT = long-course chemoradiation (5 weeks)

\*\*\*mFOLFOX6 = 8 cycles (1 cycle = 2 weeks)

\*\*\*\*mFOLFIRINOX = 8 cycles (1 cycle = 2 weeks)

# CAPOX = 5 cycles (1 cycle = 3 weeks)

Treatment is to continue for the full course of LCRT and Arm 1 or Arm 2 chemotherapy unless there is a clinical reason to stop. Following neoadjuvant chemotherapy, patients will either proceed to surgery (TME) or watch & wait (WW). Patients will be followed for 5 years or until death, whichever comes first.

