|----------------------|----------------------------------------------------------------|
| 5-Fluorouracil       | 2400 mg/m  continuous iv infusion over 46-48 hours |
| Leucovorin           | 400 mg/m  iv day 1                                 |
| Irinotecan           | 150 mg/m  iv day 1                                 |
| Oxaliplatin          | 85 mg/m  iv day 1                                  |
| Repeat every 2 weeks |                                                                |

In the PRODIGE23 trial (that used doses as detailed above except for a slightly higher dose of irinotecan at 180 mg/m^2 iv day 1), although slightly higher rates of  $\geq$  grade 3 neutropenia (2.8% vs 0) and capecitabine discontinuation (8% vs 3%;  $p < 0.02$ ) were noted during LCRT in the TNT arm, they did not impact proportion of patients undergoing subsequent surgery (92.2% vs 94.8%;  $p = 0.26$ ) perioperative morbidity or quality of life. In fact, trends towards improvement in non-therapeutic surgery (0% vs 3.7%); metastatic disease at pre-surgical staging (1% vs 4.7%) and better tolerance of subsequent adjuvant therapy ( $\geq$  grade 3 toxicities 11.7% vs 20.7%) were noted favoring the TNT arm. Importantly, the 7-year updated data from PRODIGE23 presented at ASCO 2023 demonstrated significantly better DFS, metastasis-free survival and overall survival in the TNT-arm versus the standard of care arm (68% vs. 63% DFS)[44]. These data support the use of a triplet TNT approach to improve DFS outcome for rectal cancer patients.

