**Evaluations during follow-up for WW patients (after completion of TNT with cCR and post-TNT restaging)**

| Years on study                                | Year 1
(Every 3 months) |   |   |    | Year 2
(Every 3 months) |    |    |    | Year 3
(Every 6 months) |    | Years 4-5**
(Every 6 months) |    |    |    |
|-----------------------------------------------|----------------------------|---|---|----|----------------------------|----|----|----|----------------------------|----|---------------------------------|----|----|----|
| Months after post-TNT restaging (+/- 30 days) | 3                          | 6 | 9 | 12 | 15                         | 18 | 21 | 24 | 30                         | 36 | 42                              | 48 | 54 | 60 |
| History and Physical                          | X                          | X | X | X  | X                          | X  | X  | X  | X                          | X  | X                               | X  | X  | X  |
| Sigmoidoscopy/
Proctosigmoidoscopy         | X                          | X | X | X  | X                          | X  | X  | X  | X                          | X  | X                               | X  | X  | X  |
| MRI Rectum                                    |                            | X |   | X  |                            | X  |    | X  |                            | X  |                                 | X  |    | X  |
| CT CAP                            |                            |   |   | X  |                            |    |    | X  |                            | X  |                                 | X  |    | X  |
| CEA levels                        | X                          | X |   | X  | X                          | X  |    | X  | X                          | X  | X                               | X  | X  | X  |

\*If TME completed via abdominoperineal resection – not relevant and unnecessary

\*\*MRI in years 4 through 8 would only be supported if clinically indicated by treating team.

 CT of the Chest, Abdomen and Pelvis Patients in the TME group will be followed according to NCCN guidelines.[1]

 After 36 months, CEA will be evaluated every 6 months up to five years, based on NCCN guidelines.

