### 11.2 Clinical Tumor Evaluation prior to TME

**Endoscopic exam:** The length of the tumor is defined as the difference between the distance of the proximal and distal margins in relation to the anal verge. This is best determined by flexible sigmoidoscopy. Determination of clinical complete response, near complete response and incomplete response are determined as noted in Table 11.2.1 below.

For patients who undergo TME after TNT, the clinical tumor response evaluations occur prior to determination of need for TME (residual tumor/incomplete response) and will be performed by endoscopy, MRI and digital rectal exam. For patients who elect to undergo a WW approach, the clinical tumor evaluations will be performed by endoscopy, MRI, and digital rectal exam during the post-TNT follow-up and up to 5 years after randomization or up to salvage TME, whichever occurs first. Patients will be evaluated as per the schedule of tests noted in [Section 5.0](#).

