## 12.3 Follow-up

### 12.3.1 Duration of Follow- up (Please see study calendar in section 5.0 for complete list of follow-up tests and procedures)

|                                                                                                                                              | MRI rectum                                                                                                     | Endoscopy and digital rectal exam                                   | CT chest, abdomen, pelvis                                                   | CEA                                                                                         |
|----------------------------------------------------------------------------------------------------------------------------------------------|----------------------------------------------------------------------------------------------------------------|---------------------------------------------------------------------|-----------------------------------------------------------------------------|---------------------------------------------------------------------------------------------|
| All patients who completed pre-operative protocol treatment                                                                                  | Pre-treatment, post-TNT re-staging                                                                             | Pre-treatment, post-TNT re-staging                                  | Pre-treatment, Post-TNT re-staging, annually from 5 years post-registration | Pre-treatment, every 3-6 months post-TNT in Years 1-2, every 6 months post-TNT in Years 3-5 |
| All patients who are off pre-operative protocol treatment early due to Progression of disease-                                               | As per treatment team                                                                                          | As per treatment team                                               | As per treatment team                                                       | As per treatment team                                                                       |

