### 13.3.2 Phase III Portion:

The phase III portion of this trial is designed to primarily compare disease-free survival (DFS) in patients with locally advanced rectal cancer treated with LCRT, mFOLFIRINOX, followed by a selective WW approach (Arm A) versus those who are treated with LCRT, mFOLFOX6, followed by a selective WW approach (Arm B). Phase III portion implements a group sequential design with one futility interim analysis based on a non-binding beta spending function (Rho family with  $Rho=3.2$ ), which will be performed when 50% of DFS events have been observed (143 events). The OPRA trial reported a three-year DFS rate of 76% (95% CI, 69-83%) for patients who received chemoradiotherapy followed by consolidation chemotherapy (CRT-CNCT)[47]. A total number of 285 DFS events will provide 85% power to detect an effect size of hazard ratio (HR) = 0.70 (3-year DFS rate of 82.5% in the experimental arm A) at a one-sided type I error rate of 0.025. With further assumptions of an accrual rate of 180 patients per year and a minimum of four years of follow-up, a maximum of 760 patients (380 in each arm) are required to enroll, unless the study team makes a decision of early termination due to monitoring rules specified in section of 13.4.2 or 13.5.1.

With the decision rules stated below in Section 13.4.2, this design provides the following design operation characteristics for interim analyses:

|                                                            |                                                                                 |                                                   |                                                 |
|------------------------------------------------------------|---------------------------------------------------------------------------------|---------------------------------------------------|-------------------------------------------------|
| Analyses time point                                        | If the true 3-year DFS rate is ...                                              | H1
Experimental arm: 82.5%
Control arm: 76% | H0
Experimental arm: 76%
Control arm: 76% |
| interim analysis (futility only) at 50% of events observed | Then the probability of stopping at the interim analysis due to futility is ... | 0.016                                             | 0.500                                           |

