**Phase III Portion:**

The Phase III hypothesis testing analyses will be performed on ITT population. Sensitivity analyses will be performed on mITT and PP population. At interim and final analyses, stratified Cox model will be conducted to compare DFS in the experimental arm to DFS in the control arm with stratification factors as stratum, based on all data collected at the analysis time point.

- **Interim Analysis Decision Rule:** The interim analysis will be conducted when 50% of targeted events (about 143) which is estimated around 4.5 to 4.9 years after the first patient is randomized (about 3.6 to 8.4 months after all patients are enrolled). If the observed HR (stratified by stratification factors) at interim analysis is  $> 1.00$ , we will conclude that the chance of DFS in experimental arm being superior to that in control arm is too low. The results will be presented to Alliance DSMB and NCI for potential public release.
- **Final Analysis Decision Rule:** The final DFS analysis will be performed when at least 285 DFS events are observed combining the two arms. Stratified Cox model will be conducted to compare DFS in the experimental arm A to DFS in the control arm B. If the one-sided p-value of the comparison is  $< 0.025$ , then we will conclude the DFS in the experimental arm is superior to the control arm.

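### The follow-up texts conflict (5 years, month 60, years 4 through 8), and the 285-event phase III design reproduces only if early enrollees are followed past 5 years

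*Combined protocol and SAP*

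**What the plan says.** On duration of follow-up, the current text says several things:

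- Text beneath the Schema: "Patients will be followed for 5 years or until death, whichever comes first".
- Section 11.2, for WW patients: endoscopy, MRI and digital rectal exam continue "up to 5 years after randomization or up to salvage TME, whichever occurs first".
- Section 5.0: the WW calendar counts "Months after post-TNT restaging (+/- 30 days") and the TME calendar counts from treatment, after definitive resection. Both have month 60 as their last column.
- Section 5.0, footnote to both calendars, attached to a column headed Years 4-5: "MRI in years 4 through 8 would only be supported if clinically indicated by treating team".
- Section 12.3.1: CT is listed at pre-treatment, at post-TNT restaging and "annually from 5 years post-registration". CEA stops at year 5.

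On the phase III design:

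- Section 13.3.2: 285 DFS events for 85% power at HR 0.70, one-sided 0.025. "With further assumptions of an accrual rate of 180 patients per year and a minimum of four years of follow-up", 760 patients are needed.
- Section 13.2: accrual lasts 4.2 years.
- Section 13.4.2: "The final DFS analysis will be performed when at least 285 DFS events are observed combining the two arms". No alternative based on calendar time is given.

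**The concern.** With 4.2 years of accrual and four more years after the last patient enters, the first patients contribute about 8.2 years. At that point (8.22 − 5)/4.22 = 76% of patients would be more than 5 years from randomization. The event count therefore depends on a period for which the document gives no visit or DFS assessment schedule, and which the Schema text excludes.

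A site that follows the Schema text could close a patient out at year 5. If enough sites did so and the triplet works as hypothesised, the primary analysis would wait for events that are not being collected. A replacement rule would then have to be written late, after the DSMB has seen interim DFS data. Phase III is analysed by intention to treat, so this also affects patients who leave treatment early, whose tests section 12.3.1 leaves to the treating team.

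**Working it through.** **Inputs.** Three-year DFS 76% versus 82.5%, HR 0.70, 285 events, one-sided 0.025, 380 per arm, 180 per year (13.3.2); 1:1 allocation (13.3). Accrual time A = 760/180 = 4.22 years, agreeing with 13.2. Assumed: exponential DFS, uniform accrual and no dropout (the documents give no rate).

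**1. The plan's own power.** Control hazard λc = −ln(0.76)/3 = 0.0915 per year; experimental λe = 0.70 × 0.0915 = 0.0640. Check: 0.76^0.70 = 0.825. Power at d events ≈ Φ(|ln 0.70|·√d/2 − 1.96). At d = 285: 0.3567 × 16.88/2 = 3.01, and Φ(1.05) = 0.853. Allowing for the futility look gives 0.850, as stated.

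**2. The plan's own timing, no cap.** Expected events per arm four years after accrual ends are 380·[1 − (e^(−4λ) − e^(−8.22λ))/(4.22λ)]. This gives 161.4 (control) + 122.3 (experimental) = 283.7. The 285th event is expected at 8.26 years. The same model puts 143 events at 4.46 years with no effect and 4.86 years under HR 0.70, matching the 4.5 to 4.9 years stated for the interim analysis. So the design was evidently computed without a 5-year cap.

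**3. A 5-year cap from randomization.** The maximum is 380·[(1 − e^(−5λc)) + (1 − e^(−5λe))] = 139.5 + 104.1 = 243.6 events, which is 41 short. Power there: 0.3567 × 15.61/2 − 1.96 = 0.82, and Φ(0.82) = 0.795, or 0.792 with the futility look.

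**4. The 60-month calendars.** Restaging is at study weeks 32 to 38, that is 32/52 = 0.62 to 38/52 = 0.73 years. Month 60 is therefore taken as 5.6 to 5.75 years from randomization for everyone. This is an assumption: the TME calendar starts at surgery, somewhat later. Even 5.9 years gives only 278 events.

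| Follow-up per patient | Expected events, HR 0.70 | Chance of ≥285, HR 0.70 | Power at that count | Expected events, HR 1.0 | Chance of ≥285, HR 1.0 |
|---|---|---|---|---|---|
| No cap, at 8.22 years | 284 | – | 85% | 323 | – |
| 5 years | 244 | about 0.1% | 79–79.5% | 279 | about 34% |
| 5.6–5.75 years | 267–272 | about 9% (5.6) to 17% (5.73) | 83–84% | 305–311 | about 93% (5.6) to 97% (5.73) |

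The capped rows are maxima, with every patient followed to the cap. The chances use a normal approximation to the event count (SD 12.8 for the 5-year cap, HR 0.70).

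**5. Sensitivity.**
- Control DFS: section 13.3.2 quotes an interval of 69 to 83% for the 76%. At HR 0.70 with the 5-year cap, the maximum is 309 events at 69%, 281 at 72% and 176 at 83%.
- Dropout: an assumed 1 to 3% per year lowers the 5-year-cap count to 238–227 and the uncapped count at 8.22 years to 276–261.
- Break-even: 285 expected events at HR 0.70 need a common cap of about 6.1 years, with full follow-up reached at 4.22 + 6.09 = 10.3 years.

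**The case against.** The strongest reply is that a 5-year stop is not settled. The calendar footnotes reach year 8 and the CT entry in 12.3.1 reaches past year 5. The summary of changes mentions 5 and 8 years, which is a sign of intent only, and the Schema figure is not shown. Most of the other 5-year statements are test schedules: section 11.2 limits examinations in WW patients and does not end collection of deaths or metastases. Section 9.2 refers to a survival follow-up phase, and the data submission schedule is a separate document. If 8-year follow-up is what sites operate, the shortfall disappears.

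Much of this stands. The likeliest defect is a longer follow-up rule that was not carried through the text. But the Schema sentence ends follow-up of the patient, not of a test. The footnote covers only MRI. The CT entry gives no end date, and read literally it omits the yearly CTs that the WW calendar starts at month 12. None of these tells a site to collect DFS after month 60.

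Two stronger readings are tempting and are not supported.

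- **That the plan cannot produce 285 events.** With no effect or a worse control arm it can, even under a 5-year cap. A common cap of about 6.1 years would also suffice in expectation.
- **That true power is near 0.70.** A reader might infer this by projecting the slowing of events in the cited induction-triplet trial (75.7% DFS at 3 years, 68% at 7). That trial used surgery and adjuvant therapy rather than selective WW, and the projection rests on two rounded landmarks. It also fixes an analysis date, whereas section 13.4.2 waits for events, so without a cap slower events mean delay rather than lost power. It could serve only as a labelled sensitivity assumption.

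**Conclusion.** The follow-up durations contradict each other in the current text, and the 285-event, 85%-power design holds only on the longer reading. If follow-up ends 5 years after randomization, the expected maximum falls short by 41 events and power is about 79%. If it ends at calendar month 60, the shortfall is about 13 to 18 events (285 − 272 and 285 − 267) and power is 83 to 84%.

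The loss of power is moderate and, on the calendar reading, small. The more serious consequence is the trigger, which would probably be missed exactly when the treatment effect is as hypothesised. These figures rest on constant hazards, 76% control DFS at three years, uniform accrual and no dropout. Dropout would lower every count; a worse control arm would raise them.

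**What to change.** State one rule and use it throughout: DFS events and vital status are collected on every randomised patient, including those off treatment early, until the final DFS analysis (about 8 years for the earliest enrollees). Reconcile the Schema text, section 11.2, both section 5.0 calendars with their footnotes, and section 12.3.1 with sections 13.3.2 and 13.4.2. What imaging and visits take place after year 5 is for the clinical team to decide.

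If follow-up is really meant to stop at 5 years, restate the expected events and the power (about 79 to 84%, depending on the time origin) and revise the 285-event trigger.

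A calendar date as a backstop to the trigger is optional, since event-driven timing without one is ordinary once the follow-up rule is clear.

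The cost is amendment wording and longer status follow-up for early enrollees. No additional patients are needed.
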